### Trial management

The progress of the trials will be monitored by three committees. Table 5 shows the role and scope of these committees. Trial monitoring and auditing will comprise the collation and reporting of routine trial process indicators and SAEs. Summary statistics and graphs showing trends over time will be compiled for the process indicators, and reported weekly to the trial management committee (TMC), monthly to the trial steering committee (TSC) and twice per year to the data safety and monitoring board (DSMB) in the USA.

**Table 5 Tab5:** Trial management committees

Committee	Role	Members	Frequency of meeting
Trial management committee (TMC)	Monitor all aspects of the conduct and progress of the trial, ensure that the protocol is adhered to, in particular the protocol related to the monitoring and reporting of SAEs, and take appropriate action to safeguard participants and the quality of the trial itself.	Principal investigators	Weekly
		Site principal investigators	
		Trial managers	
		Research team leads	
		Intervention team leads	
		Data managers	
Trial steering committee (TSC)	Provide overall governance and oversight of the trial and ensure that it is being conducted in accordance with the protocol and the relevant regulations. The TSC must agree the final trial protocol and any protocol amendments, and provide advice to the TMC on all aspects of the trial. Decisions about termination of the trial or substantial amendments to the protocol are the final responsibility of the TSC. The TSC comprises the sponsors and funders, NIMH being the funder and LSHTM and University of Liverpool being the sponsors of SHARE India and Pakistan, respectively. Both sponsoring institutions will be responsible for individual sites.	NIMH staff	Monthly
		Trial statistician and Data Coordinating Centre (LSHTM, UK) staff	
		Members of the TMC	
Data safety and monitoring board (DSMB)	The DSMB has been set up by NIMH, USA, to work specifically with the Global Hubs trials. The DSMB will ensure the safety of participants. The board will review and approve the study protocols, informed consent and all relevant documents and procedures. It is responsible for site monitoring and audit of the progress of the study, including recruitment and retention of participants, adverse events, SAEs and adherence to the time line of the study, and for making recommendations about the continuation, modification or termination of the study, based on the balance of adverse events and beneficial outcomes. Apart from this, the sites will submit reports twice per year with details of data collection and adverse events.	NIMH staff	Six monthly

### Ethical considerations

The trial protocols have been granted ethical approval from the respective sites, the Institutional Review Board of Human Development Research Foundation (Pakistan), Institutional Review Board of Sangath (Goa, India), Indian Council of Medical Research, Observational/Interventions Research Ethics Committee of LSHTM, UK, and the Committee of Research Ethics at University of Liverpool, UK. Lastly, both trial protocols have ethical approval granted by the Global Mental Health DSMB of NIMH, USA.

Written (or witnessed or audio recorded, if the participant is illiterate) informed consent will be mandatory for enrolment. Separate consent will be taken for participation in the qualitative study. All participants will be able to access EUC, which represents a higher quality of care than what is currently available at both sites. We will protect the confidentiality of personal data principally through procedures to separate study data and participant-identifiable data. Quantitative data gathered in the tablets for each participant at baseline will retain personal identification items to minimise errors in transcribing identities, but these will be removed before transferring the data to STATA for analysis. We will monitor the occurrence of a number of specific SAEs, which include death of the participant due to any cause, suicide attempt, violence against the participant, stillbirth, miscarriage or loss of child, stigmatisation (due to the intervention), any violence towards others, in particular the participant’s children, hospital admission due to a psychiatric problem and hospital admission of the participant or infant due to a serious medical emergency. Their detection, appropriate response (involving an independent psychiatrist responding within 3 working days, if requiring immediate response) and reporting will be governed by the standard operating procedure approved by the DSMB, which sets out the a priori criteria for unblinding of adverse events (i.e. a statistically significant difference in prevalence between the two arms). SAEs will be compiled by the data manager and a blinded summary report shared with the principal investigators, local ethics committees and the DSMB.

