### Objectives and hypothesis

The objectives of the trials are to evaluate the effectiveness and cost-effectiveness of THPP for women with moderate to severe perinatal depression in Rawalpindi, Pakistan, and Goa, India. The primary hypothesis is that the THPP intervention provided together with enhanced usual care (EUC) will be superior to EUC alone in increasing the proportion with remission from perinatal depression and reducing perinatal depressive symptoms at the 6-month postnatal follow-up. We will test secondary hypotheses that the THPP intervention is associated with a range of maternal and child outcomes (Tables 1 and 2).

**Table 1 Tab1:** Primary and secondary outcomes of the trials

	Source of data (see Table 2 for details of each measure)	
Outcomes	Measure	End point
Remission at 6 months (PHQ scores <10 and < 5) & Depression severity (PHQ scores)	Patient health questionnaire (PHQ-9)	3- and 6-month postnatal follow-up
Disability scores	WHO disability assessment schedule (WHO-DAS)	3- and 6-month postnatal follow-up
Perceived social support of the mother	Multidimensional scale of perceived social support	3- and 6-month postnatal follow-up
Rates of exclusive breastfeeding	Maternal 24-hour recall using the WHO definition of exclusive breastfeeding	3- and 6-month postnatal follow-up
Infant nutritional status	Digital scales for weight and tape measure for height (height mats)	3- and 6-month postnatal follow-up
Costs of illness	Client service receipt inventory	3- and 6-month postnatal follow-up
Serious adverse events (SAEs)	SAE form	3- and 6-month postnatal follow-up

**Table 2 Tab2:** Pakistan and India trial outcome assessments

Instrument	Description	Outcome	Contextual validity
PHQ-9	Nine-item questionnaire assessment of depressive symptoms assessed on a scale of 0 to 3	Prevalence of moderate–severe depression; mean total score	Validated in primary care [29]
WHO disability assessment schedule	12-item questionnaire for measuring functional impairment over the last 30 days. In addition, two items assess the number of days the person was unable to work in these 30 days	Total disability score; quality adjusted life years; number of days out of work	Validated for international use [36]

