Client service receipt inventory	Questionnaire to collect data on the utilisation and costs of health care and lost productivity (including that of caregivers)	Costs of illness (direct and indirect)	Previously used in the study settings, an adapted version will be used based on an international study on perinatal depression [37]
Multidimensional scale of perceived social support	12-item questionnaire to measure perceived social support of the mother	Perceived social support of the mother; total score	Used in the study settings [22]
Exclusive breastfeeding	24-hour maternal recall using the WHO definition of exclusive breastfeeding	Proportion of infants exclusively breastfed	Used in the study settings [38, 39]
Height and weight of infant	Digital scales for weight and tape measure for height (height mats)	Height in centimetres and weight in grams	Extensively used in the study settings [22, 40]
Serious adverse events (SAEs)	Specifically designed questionnaire for the trials	Proportion of SAEs	Specifically designed for the trials

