#### Enhanced usual care

Participants will receive EUC in both the intervention and control arms, as there is non-existent usual care for perinatal depression. The majority of cases of perinatal depression either remain unidentified or are classified as pregnancy blues in both settings. There is no provision of services for mothers with depression in the primary health-care system of Pakistan or in hospitals in Goa. EUC will comprise the following:Informing participants about their diagnosis of depression.Informing depressed participants about ways to seek appropriate health care (i.e. by going for assistance to their LHWs, to the primary health centre or to the tertiary health centre, which is the Institute of Psychiatry, Rawalpindi, Pakistan).In India, providing gynaecologists with the findings of the screening results for perinatal depression.Providing the primary health-care centres and the gynaecologists with the adapted WHO mhGAP treatment guidelines for perinatal depression [35].Providing an information sheet to all pregnant women about how and where to seek health care from including local Community Health Workers (CHWs), primary health facilities and tertiary care facilities, both during pregnancy and beyond.

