### Masking

Due to the nature of the intervention, it is not possible to mask participants and peers to treatment allocation. However, outcome evaluation will be masked, as all outcome measures will be administered by trained research assessment teams (outcome assessors), who are non-residents of the study area, independent of the intervention and masked to treatment allocation of the participants. Furthermore, participants will be instructed not to disclose to the outcome assessors whether they are receiving the intervention or not. During all assessments, the primary outcome measure (PHQ-9) will always be completed first to minimise the risk of bias in the event of unmasking and, if it occurs, the point of unmasking will be recorded. Sensitivity analyses will be carried out to assess the effect of unmasking on the primary outcomes. The intervention and outcome assessment teams will not have any interactions during the trial since there will be separate locations and administrative management. The assessment teams will be told that they are evaluating two interventions and that there is genuine equipoise about which one is better.

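### Stigmatisation counts as an SAE only when attributed to the intervention, so this item, and any SAE total containing it, is not comparable between arms

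*Protocol article*

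**What the plan says.** All places are in the protocol article.

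- **Ethical considerations** lists the SAEs to be monitored. One is "stigmatisation (due to the intervention" (closing bracket omitted here). By contrast, mortality is counted as "death of the participant due to any cause". The same section leaves detection, response and reporting to a DSMB-approved standard operating procedure, which is said to set the criteria for "unblinding of adverse events (i.e. a statistically significant difference in prevalence between the two arms".
- **Objectives and hypothesis**, Table 1, lists SAEs among the trial outcomes, taken from the SAE form at the 3- and 6-month visits. Table 2 gives the outcome as "Proportion of SAEs".
- **Enhanced usual care** is given in both arms. Its first component is "Informing participants about their diagnosis of depression". In India the gynaecologist also receives the screening findings.
- **Masking** states that "all outcome measures will be administered by trained research assessment teams (outcome assessors", that these assessors are masked, and that "participants will be instructed not to disclose to the outcome assessors whether they are receiving the intervention or not".
- **Interventions** says that peers, who work only in the THPP arm, are trained to detect and report SAEs.
- **Minimisation of contamination** and **Compliance analysis** allow that some control women may be exposed to THPP. The former calls regular contact between arms negligible in Pakistan.

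**The concern.** An adverse event compared between arms has to be one that either arm can record in the same way. The article uses intervention arm for the THPP arm, and enhanced usual care is common to both arms. Read that way, a THPP woman who is stigmatised can become a case, while a control woman with the same experience after learning her diagnosis is not one unless she was exposed to THPP through contamination.

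Two things are at stake. First, the item feeds a reported outcome and a significance-based trigger for unblinding. An event with a control count that is near zero by construction can push both in one direction. It also means that stigma in the control arm, which the trial itself may cause by disclosing the diagnosis, is not recorded. Second, if the question goes through the masked assessors, a woman who affirms that stigma came from the intervention has disclosed her allocation, and a woman who follows the masking instruction leaves a harm unreported. Completing the PHQ-9 first protects only the same visit, so disclosure at 3 months would precede the 6-month primary PHQ-9.

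**Working it through.** The article gives no SAE rate, SAE power or SAE significance level, so there is no planned figure to reproduce. The main check sets the definition beside its use.

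**Step 1: is the definition arm-dependent?**

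| Event | Can a THPP woman be a case? | Can a control woman be a case? |
|---|---|---|
| Death, any cause | Yes | Yes |
| Psychiatric admission | Yes | Yes |
| Stigma after disclosure of the diagnosis | Only if it is attributed to THPP | No |
| Stigma attributed to THPP | Yes | Only through contamination |

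Other items also name a cause: psychiatric admission names a psychiatric problem, and medical admission names an emergency. Those causes exist in both arms. Stigmatisation is the only item whose cause is the randomised intervention.

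**Step 2: does it enter a between-arm comparison?** Yes, through the Table 2 outcome and the unblinding criterion. The article does not say whether the criterion is applied item by item or to the total, so both are illustrated below.

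**Step 3: item-level illustration.** Inputs: 560 and 280 women allocated 1:1 (Table 4), so n = 280 per arm in Pakistan and 140 in India. For k events against 0 with equal arms, the two-sided Fisher p is 2·C(n,k)/C(2n,k), which is close to 2·(1/2)^k.

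| k v 0 | n = 280 | n = 140 |
|---|---|---|
| 5 | 0.061 | 0.060 |
| 6 | 0.030 | 0.030 |

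Six events is therefore the smallest number reaching p < 0.05 in either trial. Clustering is ignored, and the article does not name this test.

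**Step 4: how likely are six?** This depends on assumptions. Suppose true stigma is equal in both arms, and a THPP woman is counted with probability q = (true rate) × (share attributed to THPP). Then P(X ≥ 6) for X ~ Binomial(n, q) is:

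| Assumption | q | Pakistan (280) | India (140) |
|---|---|---|---|
| 1 %, all attributed | 0.01 | 6 % | 0.3 % |
| 2 %, all attributed | 0.02 | 49 % | 6 % |
| 5 %, all attributed | 0.05 | 99.5 % | 71 % |
| 2 %, half attributed | 0.01 | 6 % | 0.3 % |
| 5 %, half attributed | 0.025 | 70 % | 14 % |

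The planned losses of 20 % and 15 % (Table 4) leave 280 × 0.80 = 224 and 140 × 0.85 = 119 per arm. With all cases attributed, the 2 % and 5 % rows become 29 % and 97 % in Pakistan, and 3 % and 55 % in India.

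**Step 5: total-SAE illustration.** Assume other SAEs are equal at a background b of 5–15 % per arm, and that counted stigmatisation s is 2–5 % in THPP only. The THPP proportion is b + (1 − b)·s.

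- Largest ratio: b = 0.05, s = 0.05 gives 0.0975, a risk ratio of 0.0975/0.05 = 1.95.
- Smallest ratio: b = 0.15, s = 0.02 gives 0.167, a risk ratio of 0.167/0.15 = 1.11.

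Over this grid, a two-proportion calculation at two-sided 0.05, again ignoring clustering, puts the chance of a significant difference at about 8–58 % in Pakistan and 6–33 % in India.

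**The case against.** The strongest reply is that monitoring a harm specific to the intervention is a legitimate safety choice. A harm truly caused by THPP can occur only where THPP is received, and counting it measures real excess harm. Bias arises only if background stigma is misattributed. This stands in part. It justifies collecting the item, and it means the probabilities in the working describe assumed misattribution as much as the definition itself. It does not justify placing the item in a between-arm proportion when control-arm stigma is excluded by wording.

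A second reply is that the SAE form and operating procedure are not shown and may already ask a neutral question and assign causality elsewhere. A woman could also report stigma without naming her arm. Peers are a second reporting route, unmasking is recorded, and sensitivity analyses for its effect on the primary outcomes are planned. All of this stands against treating the masking conflict as established. The peer route does not restore balance, however, because it exists only in the THPP arm.

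A reader might also infer more than the article supports:

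- *The event cannot occur in the control arm at all.* The article allows for contamination.
- *The whole SAE comparison is unbalanced.* The other items are defined alike in both arms.
- *A false safety signal is likely.* The high figures need rates of 2–5 % and full attribution, neither of which the article gives. At 1 % the chance of six events is 6 % or less.

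**Conclusion.** The concern holds for one item and for any total that includes it. As published, stigmatisation is the only SAE defined by attribution to the intervention. The same experience can therefore count in the THPP arm and, barring contamination, not in the control arm, although both arms are exposed through disclosure of the diagnosis. Nothing in the article corrects this, and the item sits within an outcome and an unblinding criterion that both compare arms.

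The size cannot be fixed from the document. The one result that needs no assumed rate is that 6 against 0 gives p of about 0.03 in either trial, if a Fisher test is used and clustering is ignored. The probabilities of reaching that count, or of a significant total, are illustrations under stated assumptions and not predictions. The masking conflict is conditional on masked assessors asking about attribution. The definition of the primary outcome and its power are not affected.

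**What to change.** In the SAE list, the SAE form and the operating procedure, define the item as any stigmatisation experienced by the participant, with no cause in the case definition. Ask it in identical words in both arms. Have its relation to THPP judged separately and afterwards by someone outside the masked assessment team, so that assessors never need to ask about it.

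The wording should not simply replace one cause with another, such as stigma related to care for depression. That would keep attribution in the definition and could still prompt a woman to mention THPP.

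If the investigators prefer to keep the intervention-specific definition, report it as a THPP-only harm, descriptively, and exclude it from the between-arm SAE proportion and from the unblinding criterion.

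If the form or procedure already works in one of these ways, bringing the published list into line with it is enough. The cost is one line on the form and in the procedure. Under the first option somewhat more events will be recorded, because control-arm cases now count.

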## Background

Depression is one of the leading burdens of disease globally and there is a large treatment gap, especially in low- and middle-income countries (LMICs) [1, 2]. In South Asia, the prevalence of common mental disorders is reported to be among the highest in the world [3–6] ranging from 18 and 30 % in urban areas [4, 7, 8] to 28–36 % in rural areas [9–11]. In addition to constituting a burden to women’s health, disability, functioning and mortality, particularly through suicide [12, 13], perinatal depression is associated with negative child outcomes including infant under-nutrition and stunting, and has been declared a global threat to child health and development [14–16]. Perinatal depression is defined as having a depressive episode either during pregnancy or during the one-year postnatal period [17, 18].

Systematic reviews in high-income countries provide robust evidence that perinatal depression can be managed effectively with psychological treatments [19, 20]. A recent systematic review for LMICs showed the burden of perinatal depression could be reduced through mental health interventions delivered by non-specialists [21]. Apart from reducing perinatal depression, these psychological treatments have shown to improve child health outcomes like increased vaccination coverage and reduced diarrheal episodes. Such interventions have been shown to improve child health outcomes [22]. However, integrating and scaling up such interventions within the existing heath systems with them delivered by community health workers (CHWs) in LMICs is challenging because CHWs are already overburdened and are a finite human resource, and there is limited evidence of the cost-effectiveness of such interventions [2, 23, 24].

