### Exclusion criteria

Women requiring immediate inpatient care for any reason (medical or psychiatric) or who do not speak Urdu, Punjabi or Potohari (Pakistan), or Konkani, Hindi or Marathi (India) will be excluded.

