Peers will be lay women, without any mental health training background who have shown an interest or desire to help and support other women within their community. These peers will be from the same communities as the trial participants or nearby communities. All the peers will be married, mothers and fluent in the local languages of the trial settings in Pakistan and India. All peers will be identified and recruited from the local community through word of mouth, particularly through community-based key informants such as the LHWs in Pakistan, and women’s group facilitators and *anganwadi* workers (community health-care workers responsible for the well-being and nutrition of mothers and newborn children) in India.

The peers will be trained in a 5-day classroom-based workshop (approximately 4–5 hours daily). This will be followed by a 2-month internship where they can practise the content of the THPP on non-trial participants. During this time, they will receive regular monitoring and competency checks, and be supervised. The training format will be based on interactive discussions and role-playing and will cover the following topics: content of the THPP intervention, confidentiality, dealing with difficult situations, and detection and reporting of serious adverse events (SAEs). In Pakistan, the LHWs will be part of the training session that covers confidentiality for peers. This will help ensure confidentiality of the participants by both the peers and LHWs. This will be refreshed and reiterated in monthly supervision meetings. Peers will also receive training on how and when to communicate with the research teams if any of these situations arise, and to take the necessary steps to trigger the referral pathway and an assessment of the trial participant by an independent psychiatrist. Peers will be assessed, at the end of their training, on their competence using structured and standardised role-playing. This will indicate any further training needs. Only peers who achieve the desired level of competence will be selected to deliver THPP in the trials.

Peers will receive monthly group-based supervision by trained intervention facilitators (who will be part of the research teams). The monthly supervision will include revision of the THPP content through discussions and role-playing. The discussions will cover the challenges faced by peers in the field, issues around confidentiality, detection of SAEs, problem-solving and keeping peers motivated.

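### Serious adverse events that need an immediate response are given a psychiatrist response limit of 3 working days

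*Protocol article*

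**What the plan says.** The Ethical considerations section lists the SAEs to be monitored. They include death, attempted suicide, violence directed at the woman, violence towards others (her children in particular) and psychiatric admission. It says that detection, response and reporting "will be governed by the standard operating procedure approved by the DSMB", and in a parenthesis it describes the response as "involving an independent psychiatrist responding within 3 working days, if requiring immediate response".

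The section on the peer-delivered intervention also mentions this psychiatrist. Peers are taught to "trigger the referral pathway and an assessment of the trial participant by an independent psychiatrist", with no time attached.

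The Trial management section gives intervals for process indicators and SAE summaries: "reported weekly to the trial management committee (TMC), monthly to the trial steering committee (TSC) and twice per year" to the DSMB.

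**The concern.** A limit of several working days does not fit a condition that says the response must be immediate. Read literally, the most urgent events are the ones allowed to wait.

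Participants' safety is at stake, not an estimate or an error rate. The trials enrol women with PHQ-9 scores of 10 or more, and the Background links perinatal depression to "mortality, particularly through suicide". The article does not say which SAEs need an immediate response, but attempted suicide is a plausible candidate. If it is one, a psychiatrist who responded several days later would still comply with the published rule.

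**Working it through.** The article has no statistical figure to reproduce here. The check has three parts.

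**1. Can the sentence be read sensibly?**
- *The condition qualifies the time limit.* SAEs that need an immediate response have a limit of 3 working days. This is self-contradictory.
- *The condition selects which SAEs go to the psychiatrist.* Only urgent SAEs are referred, and the limit for those is 3 working days. The grammar works, but urgent events still carry the multi-day ceiling.

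A rule that treats urgent events faster needs words that are not in the text. The article does not show whether a word was dropped, a unit is wrong or the condition was inverted.

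**2. Does another section give a shorter limit for an individual event?**

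| Section | Content | Response time for one event |
|---|---|---|
| Exclusion criteria | Excludes women who need inpatient care at once; applies at entry only | None |
| Thinking Healthy Programme Peer-delivered | "Peers will also receive training on how and when to communicate with the research teams if any of these situations arise"; referral to the psychiatrist | None |
| Enhanced usual care | Tells women where to seek care | None |
| Discontinuation criterion | Loss of the baby, psychotic or manic episode | None |
| Fidelity of the intervention | Counts specialist referrals as an indicator | None |
| Trial management, Table 5 | Intervals for summary reports and meetings | None |

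**3. How long is 3 working days on the calendar?**

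Input: 3 working days (Ethical considerations). The article defines neither the working week nor whether the day of report counts, so the four conventions below are assumptions. Public holidays are ignored.

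Delay = date of the third working day minus date of report. When the report day counts, it is day 1 only if it is a working day.

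| Convention | Mon | Tue | Wed | Thu | Fri | Sat | Sun | Mean |
|---|---|---|---|---|---|---|---|---|
| Sat–Sun weekend, report day not counted | 3 | 3 | 5 | 5 | 5 | 4 | 3 | 28/7 = 4.0 |
| Sunday-only weekend, report day not counted | 3 | 3 | 3 | 4 | 4 | 4 | 3 | 24/7 = 3.4 |
| Sat–Sun weekend, report day counted | 2 | 2 | 2 | 4 | 4 | 4 | 3 | 21/7 = 3.0 |
| Sunday-only weekend, report day counted | 2 | 2 | 2 | 2 | 3 | 3 | 3 | 17/7 = 2.4 |

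Example: for a Friday report under the first convention, the working days are Monday, Tuesday and Wednesday, so the limit falls 5 days later.

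The range is 2 to 5 calendar days, and no convention gives less than 2. In the order of the rows, the limit exceeds 3 calendar days on 4, 3, 3 and 0 of the 7 possible report days.

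**The case against.** The strongest reply is that the words are a parenthesis in a condensed article that summarises an SOP the reader cannot see. Urgency tiers and emergency steps normally sit in such an SOP, and their absence from an article is not a fault. The word *within* sets a ceiling and does not forbid a faster response. The psychiatrist is only one step. Peers are trained to contact the research teams, women in both arms are told where to seek care, and Table 5 makes the trial management committee responsible for acting to safeguard participants. Some listed SAEs are hospital admissions, where care has already begun. The article does not define which events are urgent, and it offers no standard against which 3 working days is too long for an independent review.

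Most of this stands as a limit on what can be concluded. It is not shown that the actual procedure is unsafe, that any woman waited, or that the psychiatrist is the first responder. It does not rescue the sentence. Leaving detail to an SOP excuses silence, but here the article states a rule, and that rule sets a multi-day ceiling on the events it calls urgent. Judging the limit too long for those events needs no outside standard, because the article's own condition says their response must be immediate.

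**Conclusion.** The concern holds. As published, the sentence contradicts itself, and no other section of the article corrects it. It permits a delay of 2 to 5 calendar days at the psychiatrist's step, on assumed counting conventions and without holidays. That figure is a permitted maximum, not a forecast.

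The link to attempted suicide rests on the plausible but unstated assumption that such an event counts as urgent. Whether the error lies in the article or in the SOP cannot be settled from the document. No power figure, estimate or analysis changes. The point should be corrected because it concerns participants' safety and is cheap to put right.

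**What to change.** 1. Compare the sentence with the DSMB-approved SOP and correct whichever is wrong.
2. State which SAEs need an immediate response (for example, attempted suicide) and give them a separate, shorter psychiatrist response limit, set by the investigators and the DSMB.
3. Keep 3 working days at most as the outer limit for other SAEs, and only if the SOP supports it.

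If the SOP is already right, the cost is one corrected sentence in the article. If it carries the same wording, it needs a short amendment with DSMB approval. If the protocol text changes, the trial steering committee must also agree, since Table 5 says "The TSC must agree the final trial protocol and any protocol amendments". The practical cost is arranging for the independent psychiatrist to be reachable sooner for urgent events at both sites.

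### Adverse events are unblinded only on a statistically significant arm difference, which is insensitive for rare serious events and leaves the DSMB a blinded summary for a harm-benefit judgement

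*Protocol article*

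**What the plan says.** **Unblinding rule.** The protocol article, Ethical considerations, lists the SAEs to be monitored. They range from participant death and suicide attempt to violence, pregnancy or infant loss, stigmatisation, and psychiatric or medical admission. A DSMB-approved procedure governs them and sets out the "a priori criteria for unblinding of adverse events (i.e. a statistically significant difference in prevalence between the two arms"). The significance level, the test, and whether events are pooled or taken by type are not stated.

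**What the DSMB sees.** The next sentence has the data manager compile SAEs, with "a blinded summary report shared with the principal investigators, local ethics committees and the DSMB". All three recipients get the same report.

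**What the DSMB must do.** Trial management, Table 5, makes the DSMB responsible for recommending whether the study goes on, changes or stops, "based on the balance of adverse events and beneficial outcomes". It meets six-monthly.

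**How SAEs are found.** Tables 1 and 2 list an SAE form at the 3- and 6-month follow-ups, with the outcome "Proportion of SAEs". Masking says that "all outcome measures will be administered by trained research assessment teams (outcome assessors"), who are masked, so the form covers both arms. In addition, peer training covers "detection and reporting of serious adverse events (SAEs"), and monthly peer supervision takes up "issues around confidentiality, detection of SAEs, problem-solving and keeping peers motivated". Peers serve THPP women only.

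**The concern.** A board that has to weigh harms against benefits needs to see harms by arm. As printed, the arm comparison is opened only after a significance test has been passed. For the most serious events the expected counts are small, so a non-significant result says little, yet it is the reason for staying blinded. An imbalance in deaths or suicide attempts that a board would want to discuss could sit below the threshold through several reviews.

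A second, smaller point concerns the input to the test. The SAE form is common to both arms, but trained peers add a continuing source of reports in one arm. If the test uses all reported SAEs, an excess in THPP could partly reflect better detection. If it uses only the form, it could not. The article does not say which.

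**Working it through.** The protocol gives no SAE rate, significance level or power for this rule, so there is no stated figure to reproduce.

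**Inputs from the protocol.** India: 280 women at 1:1, so 140 per arm. Pakistan: 560 at 1:1, so 280 per arm. Half-way through India's recruitment there are 70 per arm.

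**Assumptions.** Two-sided Fisher exact test at 0.05. Control rates of 1%, 2%, 5% and 10%, to span single rare event types up to a pooled SAE outcome. Full enrolment without loss, which favours the rule.

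**1. What split triggers unblinding?** With equal arms of n and all k events in one arm, the two-sided p is 2 × C(n,k) / C(2n,k).

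| Split | 70 per arm | 140 per arm | 280 per arm |
|---|---|---|---|
| 5 v 0 | 0.058 | 0.060 | 0.061 |
| 6 v 0 | 0.028 | 0.030 | 0.030 |
| 11 v 3 | 0.045 | 0.051 | 0.054 |

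Five events all in one arm do not trigger unblinding at any of these sizes; six do. At 140 or 280 per arm, 11 v 3 does not trigger it either.

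**2. How often is a true doubling flagged?** Power is the sum, over all pairs of counts with a significant excess, of Bin(i; n, p) × Bin(j; n, 2p).

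| Control to THPP rate | 70 per arm | India, 140 | Pakistan, 280 (no clustering) |
|---|---|---|---|
| 1% to 2% | 0.1% | 2% | 8% |
| 2% to 4% | 2% | 8% | 21% |
| 5% to 10% | 11% | 27% | 56% |
| 10% to 20% | 30% | 59% | 90% |

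By the normal approximation, 80% power for a doubling from 1%, 2%, 5% or 10% needs about 2319, 1141, 435 or 199 women per arm.

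**3. Clustering in Pakistan.** A valid test must allow for villages. No ICC is given for SAEs. If the depression ICCs in Table 4 are borrowed (mean of 0.07 and 0.05 = 0.06) with 14 women per village, the design effect is 1 + 13 × 0.06 = 1.78 and the effective size is 280 / 1.78 = 157 per arm. That is close to India's 140, so Pakistan's power would move towards the India column.

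**4. Sources of SAE reports, side by side.** Both arms: the SAE form at two visits, by masked assessors. THPP only: peers trained and supervised in SAE detection, over ten individual and four group sessions in Pakistan or 6 to 14 individual sessions in India. No matching continuing channel is described for EUC. The text on the unblinding criterion names no source. Turning this into a bias would need detection rates in each arm, which the protocol does not give.

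**The case against.** **The governing procedure is not shown.** The article gives the criterion in a short parenthesis. The full procedure may say more, a blinded summary may mean masked arm labels, and nothing printed stops the DSMB from asking for allocation. This is fair and limits the finding to the rule as printed. But that rule names statistical significance and nothing else, and the DSMB is listed with the investigators and ethics committees as a recipient of the blinded report.

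**Low power depends on the rates assumed.** This stands in part. For a pooled SAE outcome with a control rate of 10%, a doubling is flagged with 90% power in Pakistan before clustering. The weakness is specific to rare event types, which include the gravest ones.

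**Harm is not hidden.** A reader might infer that serious events could go unnoticed. The protocol does not support that: individual SAEs receive an independent psychiatrist's response where needed, process indicators and SAEs are reported to the trial committees, and pooled counts reach the DSMB. Only the comparison between arms is withheld.

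**The test does not rest on peer reports alone.** A reader might also infer that the comparison uses events detected only by peers, or that the Table 2 SAE outcome is biased by them. Neither is supported. Table 2 gives a trial-specific questionnaire as the source, and Masking places all outcome measures with masked assessors in both arms. Deaths, pregnancy losses and admissions in EUC would plausibly be recovered at follow-up without a peer. What stands is only that the source for the unblinding test is unspecified while one arm has an extra channel.

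**Restricting the comparison to the form would do harm.** This stands. A woman who has died cannot answer a form, and the Discontinuation criterion section removes women after pregnancy or infant loss or a psychotic or manic episode, possibly before any form is completed.

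**Conclusion.** The main point holds. As printed, the unblinding criterion is a significance test that is insensitive for rare serious events, and it does not fit the DSMB's stated task of weighing harm against benefit. With a two-sided Fisher test at 0.05 (assumed), 5 v 0 never triggers it at 70 to 280 per arm. A doubling from 1% to 5% control rates (assumed) goes unflagged about 73% to 98% of the time in India and 44% to 92% in Pakistan before clustering, at full enrolment; interim reviews do worse. For a common pooled outcome the criterion performs much better, at 59% and 90% power.

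The detection point holds only as an ambiguity to resolve. Its effect cannot be sized from the protocol, and it does not touch the Table 2 outcome.

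**What to change.** Replace the significance criterion with a closed report by arm to the DSMB at each six-monthly review, prepared by an independent statistician. Investigators and ethics committees continue to receive the blinded summary.

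In the closed report:
- show SAEs by type as well as in total;
- show them by source, separating events from the masked form, or from any other channel applied alike in both arms, from events reported by peers only;
- keep deaths and events in discontinued women from both arms in the comparison, and do not limit it to events elicited by the form.

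The Table 2 outcome needs no change. The cost is revised wording in the SAE procedure and the DSMB charter, plus one additional closed table per review.
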